#### 4.5.4. Liver Function Criteria

Liver chemistry threshold stopping criteria have been designed to assure subject safety. When subjects meet the following liver chemistry threshold criteria, the subject will be not entered in the second cohort and must be permanently withdrawn from the study, and the subject monitored until liver chemistries resolve, stabilize, or return to baseline values. The subject must be permanently withdrawn from the study if he/she meets following criteria:

- ALT  $\geq$  3xULN **and** bilirubin  $\geq$  1.5xULN (>35% direct).
- ALT  $\geq$  3xULN.

Subjects with ALT  $\geq$  3xULN **and** bilirubin  $\geq$  1.5xULN (>35% direct bilirubin; bilirubin fractionation required) must be required to return to the clinic (within 24 hours) for repeat liver chemistries and additional testing, and monitored closely (with specialist or hepatology consultation recommended). This event must be reported to GSK within 24 hours of learning of its occurrence. Subjects must be monitored twice weekly until liver chemistries (ALT, AST, alkaline phosphatase, bilirubin) resolve, stabilize or return to within baseline values.

Subjects with ALT  $\geq$  3xULN must be monitored weekly until liver chemistries (ALT, AST, alkaline phosphatase, bilirubin) resolve, stabilize or return to within baseline values. This event must be reported to GSK within 24 hours of learning of its occurrence.

In all the above situations, every attempt must be made to obtain the following:

- Viral hepatitis serology including:
  - Hepatitis A IgM antibody.
  - Hepatitis B surface antigen and Hepatitis B Core Antibody (IgM).
  - Hepatitis C RNA.
  - Cytomegalovirus IgM antibody.
  - Epstein-Barr viral capsid antigen IgM antibody (or if unavailable, obtain heterophile antibody or monospot testing).
  - Hepatitis E IgM antibody (if subject resides outside the USA or Canada, or has travelled outside USA or Canada in past 3 months).
- Blood sample for pharmacokinetic (PK) analysis, obtained within 56 days of last dose. Record the date/time of the PK blood sample draw and the date/time of the last dose of investigational product prior to blood sample draw on the CRF.

- Serum creatinine phosphokinase (CPK) and lactate dehydrogenase (LDH).
- Fractionate bilirubin, if bilirubin  $\geq 1.5 \times \text{ULN}$ .

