##### **4.5.5.1. Liver Chemistry Stopping Criteria**

Liver chemistry threshold stopping criteria have been designed to assure subject safety and to evaluate liver event etiology after administration of investigational product at the first follow-up period (7 days after dose). The subject will be not entered the second cohort if any of the following liver chemistry stopping criteria is met:

1. ALT  $\geq 3 \times \text{ULN}$  and bilirubin  $\geq 2 \times \text{ULN}$   
NOTE: serum bilirubin fractionation should be performed if testing is available. If fractionation is unavailable, urinary bilirubin is to be measured via dipstick (a measurement of direct bilirubin, which would suggest liver injury).
2. ALT  $\geq 5 \times \text{ULN}$ .
3. ALT  $\geq 3 \times \text{ULN}$  if associated with the appearance or worsening of rash or hepatitis symptoms (fatigue, nausea, vomiting, right upper quadrant pain or tenderness, fever, rash or eosinophilia).
4. ALT  $\geq 3 \times \text{ULN}$  persists for  $\geq 4$  weeks.
5. ALT  $\geq 3 \times \text{ULN}$  and cannot be monitored weekly for 4 weeks.

Subjects with ALT  $\geq 3 \times \text{ULN}$  **and**  $< 5 \times \text{ULN}$  **and** bilirubin  $< 2 \times \text{ULN}$ , who do not exhibit hepatitis symptoms or rash, they can be monitored weekly for 4 weeks. See Section 13 for details on weekly follow-up procedures for these subjects.

Refer to Section 13, Liver Chemistry Follow-up Procedures, for details of the required assessments if a subject meets any of the above criteria.

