#### 4.5.5.2. QTc Withdrawal Criteria

A subject that meets the criteria below will be withdrawn from the study.

- QTcB or QTcF > 500 msec or uncorrected QT > 600 msec (machine or manual overread)
- If subject has bundle branch block then criteria is QTcB or QTcF > 530 msec

These criteria are based on an average QTc value of triplicate ECGs. If an ECG demonstrates a prolonged QT interval, obtain 2 more ECGs over a brief period, and then use the averaged QTc values of the 3 ECGs to determine whether the subject should be discontinued from the study.

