#### **10.3.2. Subject Withdrawal from Investigational Product**

This is single dose study and subject withdrawal will not apply from investigational product. However, if a subject has any safety consideration after his/her first dose (e.g. clinically significant deterioration in cognition, abnormal results from safety lab tests or liver function tests) he/she will not be enrolled into the next dose group.

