## **13. LIVER CHEMISTRY FOLLOW-UP PROCEDURES**

Refer to the diagram in [Appendix 1](#) for a visual presentation of the procedures listed below.

The procedures listed below are to be followed if a subject meets any of the liver chemistry stopping criteria defined in Section [4.5.5.1](#):

- Immediately and permanently withdraw the subject from investigational product
- Notify the GSK medical monitor within 24 hours of learning of the abnormality to confirm the subject's investigational product cessation and follow-up.
- Complete the "Safety Follow-Up Procedures" listed below.

- Complete the liver event case report forms. If the event also meets the criteria of an SAE (see Section 12.2), the SAE data collection tool will be completed separately with the relevant details.
- Upon completion of the safety follow-up permanently withdraw the subject from the study and do not rechallenge with investigational product.

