**Safety Follow-Up Procedures for subjects with ALT  $\geq 3$ xULN and bilirubin  $\geq 2$ xULN (Stopping Criterion #1):**

- This event is considered an SAE (see Section 12.2). Serum bilirubin fractionation should be performed if testing is available. If fractionation is unavailable, urinary bilirubin is to be measured via dipstick (a measurement of direct bilirubin, which would suggest liver injury).
- Make every reasonable attempt to have the subjects return to the clinic (within 24 hours) for repeat liver chemistries, additional testing and to be monitored closely (with specialist or hepatology consultation recommended).
- Monitor subjects twice weekly until liver chemistries (ALT, AST, alkaline phosphatase, bilirubin) resolve, stabilize or return to within baseline values.

**Safety Follow-Up Procedures for subjects with ALT  $\geq 5$ xULN or ALT  $\geq 3$ xULN who have hepatitis symptoms or rash, can't be monitored for 4 weeks or have elevations that persist  $\geq 4$  weeks (Stopping Criteria #2 - #5):**

- Make every reasonable attempt to have the subject return to the clinic within 24-72 hrs for repeat liver chemistries and additional testing.
- Monitor subjects weekly until liver chemistries (ALT, AST, alkaline phosphatase, bilirubin) resolve, stabilize or return to within baseline values.

**Safety Follow-Up Procedures for subjects with ALT  $\geq 3$ xULN and  $< 5$ xULN and bilirubin  $< 2$ xULN, who do not exhibit hepatitis symptoms or rash:**

- Notify the GSK medical monitor within 24 hours of learning of the abnormality to discuss subject safety.
- Liver chemistries (ALT, AST, alkaline phosphatase, bilirubin) can be monitored weekly for up to 4 weeks.
- If at any point these subjects meet the liver chemistry stopping criteria (outlined in Section 4.5.5.1), perform additional testing and continue safety follow-up until liver chemistries resolve, stabilize or return to baseline values.
- After 4 weeks of monitoring, if ALT  $< 3$ xULN and bilirubin  $< 2$ xULN, subjects must be monitored twice monthly until liver chemistries normalize or return to within baseline values.

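### Section 4.5.4 contradicts Sections 4.5.5.1, 10.3.2 and 13 on liver findings: one ALT value triggers permanent study withdrawal under one rule and weekly monitoring under the other

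*Protocol*

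**What the plan says.** Section 4.5.4 lists two liver criteria: ALT at or above 3xULN with bilirubin at or above 1.5xULN (more than 35% direct), and ALT at or above 3xULN alone. Of both it says: "The subject must be permanently withdrawn from the study if he/she meets following criteria". It also bars entry to the second cohort and says the subject "must be permanently withdrawn from the study, and the subject monitored until liver chemistries resolve, stabilize, or return to baseline values".

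Section 4.5.5.1 sets a different consequence: "The subject will be not entered the second cohort if any of the following liver chemistry stopping criteria is met". Its five criteria are:

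1. ALT at or above 3xULN with bilirubin at or above 2xULN
2. ALT at or above 5xULN
3. ALT at or above 3xULN with rash or hepatitis symptoms
4. ALT at or above 3xULN lasting 4 weeks or more
5. ALT at or above 3xULN where weekly monitoring for 4 weeks is not possible

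For ALT from 3 to below 5xULN with bilirubin below 2xULN, it says of subjects "who do not exhibit hepatitis symptoms or rash, they can be monitored weekly for 4 weeks".

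Section 13 repeats that for the same group: liver chemistries "can be monitored weekly for up to 4 weeks". For subjects who do meet a 4.5.5.1 criterion, it orders immediate withdrawal from investigational product, and then: "Upon completion of the safety follow-up permanently withdraw the subject from the study and do not rechallenge with investigational product".

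Section 10.3.2 says: "This is single dose study and subject withdrawal will not apply from investigational product". It adds that a subject with a safety consideration, abnormal liver tests among the examples, is not enrolled in the next dose group.

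**The concern.** These are instructions that a site must act on within a day: 4.5.4 requires a report within 24 hours, and Section 13 requires notice to the medical monitor within 24 hours. If two sections give opposite answers for one laboratory value, sites will act differently and each can cite the protocol.

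Three things would then vary for reasons unrelated to the drug: who is withdrawn, how intensively a liver signal is worked up, and what the disposition tables record. In dose groups of 6 to 10 subjects, safety is judged case by case, so inconsistent handling of a single case matters.

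Neither amendment listed in Appendix 7 changes 4.5.4, so this is current text and not a remnant of a superseded version.

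**Working it through.** The plan states no figure to reproduce. The check compares the two rules as logical conditions.

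**Inputs.** All values are multiples of ULN. S = hepatitis symptoms or rash; P = ALT at or above 3 for 4 weeks or more; M = weekly monitoring possible.

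- Rule A (Section 4.5.4): ALT ≥ 3. The criterion with bilirubin ≥ 1.5 is a subset of this, so it affects work-up but not the withdrawal decision.
- Rule B (Section 4.5.5.1, followed by Section 13): ALT ≥ 5, or ALT ≥ 3 together with any of bilirubin ≥ 2, S, P or not M.

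**Step 1: does B ever stop a subject whom A does not?** No. Each of the five B criteria contains ALT ≥ 3 or, for ALT ≥ 5, implies it. B therefore lies wholly inside A. If A is applied as written, the B thresholds have no separate effect.

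**Step 2: where does A withdraw and B not stop?** Removing B from A leaves 3 ≤ ALT < 5, bilirubin < 2, no S, no P, and M true. The upper bilirubin limit of this zone is 2, not 1.5.

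**Step 3: when do the rules disagree?** Section 4.5.5.1 refers to the follow-up 7 days after dosing. If the raised ALT is first seen then, criterion 4 cannot be met before day 7 + 28 = day 35. The rules conflict on the day the site must act. They converge only if ALT stays at or above 3 until about day 35, or if another criterion is met first.

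**Step 4: worked cases** (no symptoms, monitoring possible, no persistence yet, bilirubin more than 35% direct where raised).

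| ALT / bilirubin | Section 4.5.4 | Sections 4.5.5.1 and 13 |
|---|---|---|
| 2.9 / 1 | Not met | Not met |
| 4 / 1 | Permanent study withdrawal; weekly monitoring | No criterion met; weekly monitoring for up to 4 weeks |
| 4 / 1.9 | Permanent study withdrawal; return within 24 hours; twice weekly; autoimmune serology and liver imaging required | No criterion met; weekly for up to 4 weeks; those tests optional |
| 8 / 1.9 | As the row above | Criterion 2 met; return within 24 to 72 hours; weekly; those tests optional |
| 4 / 2 | Permanent study withdrawal; twice weekly; those tests required | Criterion 1 met; twice weekly; those tests required |

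Rows 2 and 3 show the conflict over withdrawal. Rows 3 and 4 show the conflict from the bilirubin cut, which holds for any ALT ≥ 3 with bilirubin from 1.5 to below 2.

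Work-up differs in row 2 as well. Section 4.5.4 seeks viral hepatitis serology and a PK sample in all its situations, whereas Section 13 asks for these only when a stopping criterion is met.

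**Step 5: consequences side by side.**

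- 4.5.4: out of the study permanently and not entered in the second cohort, with liver monitoring continuing.
- 4.5.5.1: not entered in the second cohort.
- 13: withdrawn from product at once, then from the study once safety follow-up is complete.
- 10.3.2: withdrawal from product does not apply; no next dose group.

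The timing of study withdrawal is deferred in Section 13 and not deferred in 4.5.4. The order in Section 13 to withdraw from product is one that 10.3.2 says cannot arise.

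**The case against.** The strongest reply is that the practical gap is small. Each subject receives one dose per dose group, so no treatment is running that could be stopped or continued. In the conflict zone with bilirubin below 1.5xULN, both rules call for weekly monitoring and contact with the sponsor within 24 hours. A return to a later group requires meeting the entry criteria again, which exclude ALT above 1.5xULN, and 10.3.2 already bars a subject with abnormal liver tests. All of this stands, and it limits the effect on re-dosing. It does not resolve the opposite instructions on study withdrawal or the different work-up.

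A reader might infer that withdrawal removes safety follow-up. The documents do not support this. Section 4.5.4 keeps liver monitoring going, Section 13 puts study withdrawal after the safety follow-up, 10.3.1 asks for every effort at exit evaluations, and 12.6 follows adverse events to resolution or stabilisation. PK and MMSE are not simply lost either: 4.5.4 and 13 seek a PK sample after a liver event, and the 10.3.1 list includes cognitive tests. What that list omits and neither liver section supplies is MRI and anti-drug antibody.

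A reader might also extend the contradiction to the QTc rule: "A subject that meets the criteria below will be withdrawn from the study". No other section contradicts it. Sections 4.5.5 and 10.3.2 bar the next dose group but do not say that this is the only consequence.

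**Conclusion.** The contradiction is real and can be read directly from the current text. It covers ALT from 3 to below 5xULN with bilirubin below 2xULN, no symptoms or rash, no persistence for 4 weeks or more, and weekly monitoring possible. A second conflict, over monitoring frequency and required tests, covers ALT at or above 3xULN with bilirubin from 1.5 to below 2xULN when more than 35% is direct. The consequence of a liver finding is also stated inconsistently across four sections.

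How many subjects this would affect cannot be said, because the protocol gives no rate of ALT elevation. Expressing one withdrawal as a share of a dose group would presuppose both an event and the loss of all its later data, and the documents establish neither.

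Nor do they support a claim that the results would favour subjects who tolerated the drug. The primary CSF endpoint is sampled within 22 hours, before the 7-day liver check, and Sections 6.3.2.1.1 and 6.3.2.4 restrict no analysis to completers.

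One related point is open: the protocol does not say whether the scheduled day 7 and day 56 assessments continue after a safety withdrawal. The conclusion rests on reading each section as written. It takes no position on which threshold or consequence is clinically right.

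**What to change.** Reconcile Sections 4.5.4, 4.5.5.1, 10.3.2 and 13 into a single liver rule with one set of ALT and bilirubin thresholds, one monitoring and work-up schedule, and one stated consequence. State that rule once and have the other sections refer to it. The clinical content is for the sponsor's safety team.

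In the same amendment, state whether the scheduled day 7 and day 56 assessments continue after a safety withdrawal, whether for a liver or a QTc finding, and say explicitly what applies to MRI and anti-drug antibody, which the 10.3.1 exit list omits.

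The cost is amendment wording and notice to sites. The reconciliation itself requires no new visit, sample or change in sample size.

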#### **4.5.5. Dose Adjustment/Stopping Safety Criteria**

Subjects will be given a single dose administration in each dose group. If a subject fails the safety criteria after administered GSK933776, he/she will be not considered to enroll in next dose (cohort) group.

##### **4.5.5.1. Liver Chemistry Stopping Criteria**

Liver chemistry threshold stopping criteria have been designed to assure subject safety and to evaluate liver event etiology after administration of investigational product at the first follow-up period (7 days after dose). The subject will be not entered the second cohort if any of the following liver chemistry stopping criteria is met:

1. ALT  $\geq 3 \times \text{ULN}$  and bilirubin  $\geq 2 \times \text{ULN}$   
NOTE: serum bilirubin fractionation should be performed if testing is available. If fractionation is unavailable, urinary bilirubin is to be measured via dipstick (a measurement of direct bilirubin, which would suggest liver injury).
2. ALT  $\geq 5 \times \text{ULN}$ .
3. ALT  $\geq 3 \times \text{ULN}$  if associated with the appearance or worsening of rash or hepatitis symptoms (fatigue, nausea, vomiting, right upper quadrant pain or tenderness, fever, rash or eosinophilia).
4. ALT  $\geq 3 \times \text{ULN}$  persists for  $\geq 4$  weeks.
5. ALT  $\geq 3 \times \text{ULN}$  and cannot be monitored weekly for 4 weeks.

Subjects with ALT  $\geq 3 \times \text{ULN}$  **and**  $< 5 \times \text{ULN}$  **and** bilirubin  $< 2 \times \text{ULN}$ , who do not exhibit hepatitis symptoms or rash, they can be monitored weekly for 4 weeks. See Section 13 for details on weekly follow-up procedures for these subjects.

Refer to Section 13, Liver Chemistry Follow-up Procedures, for details of the required assessments if a subject meets any of the above criteria.

#### 4.5.5.2. QTc Withdrawal Criteria

A subject that meets the criteria below will be withdrawn from the study.

- QTcB or QTcF > 500 msec or uncorrected QT > 600 msec (machine or manual overread)
- If subject has bundle branch block then criteria is QTcB or QTcF > 530 msec

These criteria are based on an average QTc value of triplicate ECGs. If an ECG demonstrates a prolonged QT interval, obtain 2 more ECGs over a brief period, and then use the averaged QTc values of the 3 ECGs to determine whether the subject should be discontinued from the study.

#### 4.5.5.3. Blood coagulation and Platelets

- INR > 2
- Platelet count < 124,000/mm^3, or ≥ 40% change from baseline values

This protocol allows some alteration from the currently outlined dosing schedule, but the predicted maximum will not exceed 6mg/kg.

The decision to proceed to the next dose level of GSK933776, will be decided by the GSK Study Team and the investigator based on total and free amyloid steady levels in CSF and plasma, safety and tolerability data obtained at the prior dose level. The actual doses to be administered may be adjusted either an increase or a decrease in the planned doses.

The dosing schedule may also be adjusted to expand a dosing groups to further evaluate pharmacodynamic and safety findings at a given dose level, or to add dose group to evaluate up to 2 additional dose levels. The study procedures for these additional subject(s) or dose group(s) will be the same as that described for other study subjects.

#### 4.5.5.4. Other Dose Adjustment/Stopping Safety Criteria

If new microbleeds are detected by MRI in two separate individuals, further dosing will be stopped to allow re-assessment of the safety of GSK933776 in the subjects that were already exposed to the experimental compound.

#### 4.6. Time and Events Table

| Procedure                                                                                               | Screening 
(up to 30 days prior to Day 1) | In-house CSF sample collection phase |                                 |     |     |     |     |     |     |     |     |      |      |                                  |      |      |      |      |      |      |      |      |      | Follow –up  |      |
|---------------------------------------------------------------------------------------------------------|----------------------------------------------------------|--------------------------------------|---------------------------------|-----|-----|-----|-----|-----|-----|-----|-----|------|------|----------------------------------|------|------|------|------|------|------|------|------|------|-------------------------|------|
|                                                                                                         |                                                          | Pre Baseline                         | Baseline Samplings  |     |     |     |     |     |     |     |     |      | Dose | Post dose samplings  |      |      |      |      |      |      |      |      |      |                         |      |
|                                                                                                         |                                                          |                                      | 1 h                             | 2 h | 3 h | 4 h | 5 h | 6 h | 7 h | 8 h | 9 h | 10 h |      | 11 h                             | 12 h | 13 h | 14 h | 15 h | 16 h | 17 h | 18 h | 19 h | 20 h | 21 h                    | 22 h |
| Procedures for all subjects on outpatient visits                                                        |                                                          |                                      |                                 |     |     |     |     |     |     |     |     |      |      |                                  |      |      |      |      |      |      |      |      |      |                         |      |
| Informed Consent                                                                                        | x                                                        |                                      |                                 |     |     |     |     |     |     |     |     |      |      |                                  |      |      |      |      |      |      |      |      |      |                         |      |
| Demographics                                                                                            | x                                                        |                                      |                                 |     |     |     |     |     |     |     |     |      |      |                                  |      |      |      |      |      |      |      |      |      |                         |      |
| Medical/medication/drug/alcohol history                                                                 | x                                                        |                                      |                                 |     |     |     |     |     |     |     |     |      |      |                                  |      |      |      |      |      |      |      |      |      |                         |      |
| Concomitant Medication Review                                                                           |                                                          |                                      |                                 |     |     |     |     |     |     |     |     |      |      |                                  |      |      |      |      |      |      |      |      |      |                         |      |
| Height and Weight                                                                                       | x                                                        |                                      |                                 |     |     |     |     |     |     |     |     |      |      |                                  |      |      |      |      |      |      |      |      |      |                         |      |
| Full Physical Exam                                                                                      | x                                                        |                                      |                                 |     |     |     |     |     |     |     |     |      |      |                                  |      |      |      |      |      |      |      |      |      |                         |      |
| Neurological Exam                                                                                       | x                                                        |                                      |                                 |     |     |     |     |     |     |     |     |      |      |                                  |      |      |      |      |      |      |      |      |      |                         |      |
| Hachinski Ischaemia Assessment                                                                          | x                                                        |                                      |                                 |     |     |     |     |     |     |     |     |      |      |                                  |      |      |      |      |      |      |      |      |      |                         |      |
| HAM D Assessment                                                                                        | x                                                        |                                      |                                 |     |     |     |     |     |     |     |     |      |      |                                  |      |      |      |      |      |      |      |      |      |                         |      |
| DSM IV Criteria Assessment                                                                              | x                                                        |                                      |                                 |     |     |     |     |     |     |     |     |      |      |                                  |      |      |      |      |      |      |      |      |      |                         |      |
| MMSE                                                                                                    | x                                                        |                                      |                                 |     |     |     |     |     |     |     |     |      |      |                                  |      |      |      |      |      |      |      |      |      |                         | x    |
| Estimated creatinine clearance                                                                          | x                                                        |                                      |                                 |     |     |     |     |     |     |     |     |      |      |                                  |      |      |      |      |      |      |      |      |      |                         |      |
| HIV, Hep B and Hep C, Syphilis screen                                                                   | x                                                        |                                      |                                 |     |     |     |     |     |     |     |     |      |      |                                  |      |      |      |      |      |      |      |      |      |                         |      |
| Screening CSF sample for safety assessments and amyloid beta 1-42, total tau and phosphorylated tau 181 | x                                                        |                                      |                                 |     |     |     |     |     |     |     |     |      |      |                                  |      |      |      |      |      |      |      |      |      |                         |      |
| Screening serum sample for safety assessment                                                            | x                                                        |                                      |                                 |     |     |     |     |     |     |     |     |      |      |                                  |      |      |      |      |      |      |      |      |      |                         |      |
| MRI Scan                                                                                                | x                                                        |                                      |                                 |     |     |     |     |     |     |     |     |      |      |                                  |      |      |      |      |      |      |      |      | x    |                         | x    |

| Procedure                                                                       | Screening 
(up to 30 days prior to Day 1) | In-house CSF sample collection phase |                                                                          |     |     |     |     |     |     |     |     |      |                                  |      |      |      |      |      |      |      |      |      |      | Follow –up  |      |        |
|---------------------------------------------------------------------------------|----------------------------------------------------------|--------------------------------------|--------------------------------------------------------------------------|-----|-----|-----|-----|-----|-----|-----|-----|------|----------------------------------|------|------|------|------|------|------|------|------|------|------|-------------------------|------|--------|
|                                                                                 |                                                          | Pre Baseline                         | Baseline Samplings                                           |     |     |     |     |     |     |     |     | Dose | Post dose samplings  |      |      |      |      |      |      |      |      |      |      |                         |      |        |
|                                                                                 |                                                          |                                      | 1 h                                                                      | 2 h | 3 h | 4 h | 5 h | 6 h | 7 h | 8 h | 9 h |      | 10 h                             | 11 h | 12 h | 13 h | 14 h | 15 h | 16 h | 17 h | 18 h | 19 h | 20 h | 21 h                    | 22 h | 7 days |
| Procedures for all subject in the clinical unit and on outpatient visits |                                                          |                                      |                                                                          |     |     |     |     |     |     |     |     |      |                                  |      |      |      |      |      |      |      |      |      |      |                         |      |        |
| Pharmacodynamics plasma – beta amyloid total and free levels                    |                                                          | x                                    |                                                                          |     |     | x   | x   | x   | x   | x   | x   | x    | x                                | x    | x    | x    | x    | x    | x    | x    | x    | x    | x    | x                       | x    |        |
| Pharmacokinetic Sampling Blood                                                  |                                                          | x                                    |                                                                          |     |     |     |     |     |     |     | x   | x    | x                                | x    | x    |      | x    |      | x    |      | x    |      | x    | x                       | x    |        |
| 12 – lead ECG                                                       | x                                                        | x                                    |                                                                          |     |     |     |     |     |     |     |     |      |                                  |      |      |      |      |      |      |      |      |      | x    | x                       | x    |        |
| Vital Signs                                                       | x                                                        | x                                    |                                                                          |     |     |     |     |     |     |     |     |      |                                  |      |      |      |      |      |      |      |      |      | x    | x                       | x    |        |
| Hema/Chem/Urinalysis tests                                                      | x                                                        | x                                    |                                                                          |     |     |     |     |     |     |     |     |      |                                  |      |      |      |      |      |      |      |      |      |      | x                       | x    |        |
| Anti-GSK933776 antibody Sampling                                                |                                                          | x                                    |                                                                          |     |     |     |     |     |     |     |     |      |                                  |      |      |      |      |      |      |      |      |      |      | x                       | x    |        |
| Urine Drug/Alcohol Screen                                                       | x                                                        | x                                    |                                                                          |     |     |     |     |     |     |     |     |      |                                  |      |      |      |      |      |      |      |      |      |      |                         |      |        |
| Brief Physical Exam                                                             |                                                          | x                                    |                                                                          |     |     |     |     |     |     |     |     |      |                                  |      |      |      |      |      |      |      |      |      |      | x                       | x    |        |
| Serum beta hcg (women < 2 years postmenopausal only)                | x                                                        | x                                    |                                                                          |     |     |     |     |     |     |     |     |      |                                  |      |      |      |      |      |      |      |      |      |      | x                       |      |        |
| Adverse Event Review                                                            |                                                          |                                      | -----                                                                    |     |     |     |     |     |     |     |     |      |                                  |      |      |      |      |      |      |      |      |      |      |                         | x    | x      |
| Pharmacogenetic Sampling AD patients                                            |                                                          |                                      | -----Collect PGx sample after the start dosing (preferred on Day 1)----- |     |     |     |     |     |     |     |     |      |                                  |      |      |      |      |      |      |      |      |      |      |                         |      |        |
| Procedures for all subjects in the clinical unit.                        |                                                          |                                      |                                                                          |     |     |     |     |     |     |     |     |      |                                  |      |      |      |      |      |      |      |      |      |      |                         |      |        |
| Admission to Unit                                                               |                                                          | x                                    |                                                                          |     |     |     |     |     |     |     |     |      |                                  |      |      |      |      |      |      |      |      |      |      |                         |      |        |
| Insert CSF catheter                                                             |                                                          | x                                    |                                                                          |     |     |     |     |     |     |     |     |      |                                  |      |      |      |      |      |      |      |      |      |      |                         |      |        |
